**Methods:**

This study is a large-scale, multi-center, parallel-group, open-label, randomized controlled clinical trial. This study will be conducted from September 2019 to December 2025. A total of 2820 patients with coronary heart disease will be recruited from two clinical sites and equally randomized into three groups: the intervention group and two control groups. All participants will be informed of six-time points (at 1, 3, 6, 12, 24, and 36 months after discharge) for follow-up visits. Over a course of 36 months, patients who are randomized to the intervention arm will receive individualized interventions delivered by a fully functional *iCARE* that using various visualization methods such as comics, videos, pictures, text to provide individualized interventions in addition to standard care. Patients randomized to control group 1 will receive interventions delivered by a modified *iCARE* that only presented in text in addition to routine care. Control group 2 will only receive routine care. The primary outcome is the incidence of major cardiovascular events within 3 years of discharge. Main secondary outcomes include changes in health behaviors, medication adherence, and cardiovascular health score.

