### Settings and participants

Eligible patients will be recruited from three cardiac wards and one emergency ward in two university affiliated hospitals. All participants will be followed up for a total of three years (with six time-points for data collection). Patients will be included in the study if they: (a) are 18 years or older; (b) have a documented diagnosis of CHD including acute myocardial infarction (AMI), acute coronary syndrome (ACS), or undertake a percutaneous coronary intervention (PCI) either as emergency or elective procedures; (c) have at least one smartphone with Android system and use it daily, and (d) agree to participate. We choose smart phones with android system to install the *iCARE* as they are more popular and affordable in China [31].

The exclusion criteria include: patients who are (1) with a history of psychiatric and neurological disorders; (2) unable to speak or understand Mandarin; (3) illiterate; (4) with impaired bilateral hearing, or visual impairment which limits the use of smartphone; (5) with contraindications or severe physical disabilities that limit patients from participation; (6) with severe medical conditions; and (7) participating in other ongoing clinical trials or prospective cohort studies. Additional exclusion criteria will be applied if patients are not able to understand the procedure and the aims of the study after full explanation, or not able to fill in the questionnaires during the baseline visits.

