### Randomization and blinding

In this proposed study, three versions of *iCARE* apps will be installed on participant’s smart phone based on their group assignment (Additional file 1). Study investigators will assist participants in each group to download, register and log into the designated *iCARE* app:*iCARE*-1: is fully functional with individualized interventions delivered via multiple visual displays such as comics, videos, pictures, and text to address all the factors in the CAM model plus routine care;*iCARE*-2: is fully functional but all interventions are delivered only via text which did not address all factors in the CAM model plus routine care;*iCARE*-3: has limited function which only allows patients for daily data entry.

After baseline data collection, participants will be randomized to one of the three groups: the intervention group (*iCARE*-1 plus routine care), the control group 1 (*iCARE*-2 plus routine care), or the control group 2 (*iCARE*-3 plus routine care), following stratified block randomization. The randomization will be computer-generated by a statistician who will not have any active involvement in the study. The block size will be set at 15 with the allocation ratio set at 1:1:1 to ensure balance among three study groups. Participants will be stratified by 4 wards and their smoking status. The randomization assignment will be generated randomly, numbered consecutively, and will be kept in a sealed, opaque envelope. Patient assignment will be revealed to study researchers only after participants completed their baseline visit. This proposed study is an open-labeled trial as participants are fully aware of their intervention allocation, and the group assignments were known to study investigators. However, researchers who perform data analysis, and clinical staff who conduct laboratory testing will be unaware of the group assignment.

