### Sample size calculation and power analysis

Based on previous studies [3, 4, 52], we anticipated that the 3-year incidence rate for cardiovascular events is 10% for patient with CHD. We estimated that a total of 2256 participants (752 per group) would provide 80% power to detect a 40% relative reduction [53] in MACEs (the incidence of MACEs is 10% for the control group and 6% for the intervention group, hazard ratio is 0.6), with 2-sided testing and alpha set at 0.05, and following a Cox proportional hazards regression method. According to previous studies [34, 54] and based on our pilot study, we anticipated a maximum attrition rate of 20% among all enrolled patients. Therefore, a total sample size of 2820 participants (940 per group) are needed in the present study.

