### Data analyses

For baseline characteristics, categorical variables will be described as frequencies and proportions; continuous variables will be described as means and standard deviations, or medians and interquartile ranges where appropriate. Differences in baseline characteristics between the control and intervention groups will be detected using ANOVA test (continuous variables) or χ^2^ test (categorical variables) where appropriate.

Comparison of between group differences on the primary outcome will be performed according to both the intention-to-treat and the per-protocol principles. Simple χ^2^ analyses will be used to evaluate the main effect of the intervention on the MACEs at the end of the intervention period. Cox proportional hazards regression (with time to first event) will be used to estimate hazard ratios (HRs) comparing MACEs among three groups, by considering study group as an independent variable adjusted for covariates that are used for stratification (i.e., study sites, smoking status). The HRs and 95% *CI* will be calculated. Significant differences will be reported at the alpha level of 0.05 (two-sided).

All analyses related to secondary outcomes of the study are exploratory. The results of the analysis will be used to clarify the interpretation of the results related to the primary analysis, which include: changes in the proportion of adherence to health behaviors and medication, changes in anthropometry and biochemical parameters, etc. The mixed models and multilevel logistic regression models will be used to assess the differences in secondary outcomes between groups. Meanwhile, we will also explore whether the effects of intervention on the primary and secondary outcomes are consistent or not across subgroups of interest. Sensitive analyses will also be conducted.

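### The Cox model claims to adjust for the stratification factors but names study site, whereas randomisation is stratified by ward

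*Protocol article*

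**What the plan says.** Three parts of the protocol article bear on this point.

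- **Randomization and blinding** names the stratification factors: "Participants will be stratified by 4 wards and their smoking status". It adds: "The block size will be set at 15 with the allocation ratio set at 1:1:1".
- **Settings and participants** says where the wards are. Patients are "recruited from three cardiac wards and one emergency ward in two university affiliated hospitals". The abstract (Methods) describes the same structure as patients who "will be recruited from two clinical sites and equally randomized into three groups".
- **Data analyses** specifies the Cox model, with time to first event and study group as the independent variable, "adjusted for covariates that are used for stratification (i.e., study sites, smoking status".

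Hospital or site is not named as a stratification factor anywhere else, and ward is not named in the analysis.

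**The concern.** The analysis section sets a sound rule, to adjust for what was used to stratify, and then spells the rule out with a factor that the randomisation section does not use. One analyst, following the listed covariates, would fit a two-level site term. Another, following the rule, would fit a four-level ward term. Both could say that they followed the protocol.

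At stake is an unambiguous covariate set for the model of the primary outcome, fixed before data are seen. If wards within a hospital differ in event risk, leaving ward out of a Cox model pulls the hazard ratio slightly toward 1 and gives up a little power.

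**Working it through.** **1. The plan's own figure.** Inputs from the sample size section: "the incidence of MACEs is 10% for the control group and 6% for the intervention group, hazard ratio is 0.6"; 80% power; "with 2-sided testing and alpha set at 0.05, and following a Cox proportional hazards regression method". For a pairwise 1:1 comparison (Schoenfeld):

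events = 4(1.960 + 0.842)² / (ln 0.6)² = 4 × 7.849 / 0.2609 = 120.3

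The two arms together contribute 0.10 + 0.06 = 0.16 events per pair of patients, so n per arm = 120.3 / 0.16 = 752. With 20% attrition, 752 / 0.80 = 940 per arm and 3 × 940 = 2820 in total. The stated figures reproduce. Neither site nor ward enters the formula, so the choice between them leaves the sample size unchanged.

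**2. What the literal model leaves out.** Ward has 4 levels (3 degrees of freedom) and site has 2 (1 degree of freedom). Because wards are nested in hospitals, the site term omits 3 − 1 = 2 degrees of freedom of within-hospital ward differences, whichever way the wards are divided. Four wards in two hospitals can split only as 2 + 2 or 1 + 3, so at least one hospital holds two or more wards that the site term merges. If smoking has two levels at randomisation (the number is not stated), there are 4 × 2 = 8 randomisation strata against 2 × 2 = 4 site-by-smoking cells.

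**3. Size, by simulation.** From the plan: 2820 patients, three arms, blocks of 15 within ward and smoking strata, hazard ratio 0.6, three years of follow-up. Assumed, because the documents do not give them: equal ward sizes, 40% smokers, hazard multipliers of 1.3 for smokers and 0.87 for others, 20% of patients with censoring times spread uniformly over the three years, the 3-year ward risks, and the assignment of wards to hospitals. Both models were fitted to the same datasets, with site or ward as a covariate alongside smoking. There were 1500 runs per row, and the estimated hazard ratio is the exponential of the mean log hazard ratio.

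| Assumed ward risks (%) | Assumed split | Power, site / ward | Estimated HR, site / ward | Type I error, site / ward |
|---|---|---|---|---|
| 8, 8, 8, 16 | fourth ward alone | 85.5% / 85.5% | 0.598 / 0.598 | 5.1% / 5.1% |
| 5, 8, 11, 16 | fourth ward alone | 85.3% / 85.7% | 0.600 / 0.599 | 5.1% / 5.1% |
| 4, 7, 10, 20 | fourth ward alone | 85.2% / 85.1% | 0.601 / 0.600 | 4.5% / 4.5% |
| 8, 8, 8, 16 | two and two | 85.2% / 85.5% | 0.599 / 0.598 | 4.9% / 5.1% |
| 4, 8, 4, 24 (extreme) | two and two | 82.6% / 84.5% | 0.612 / 0.604 | 4.8% / 5.5% |

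The largest differences are 84.5 − 82.6 = 1.9 points of power and 0.612 − 0.604 = 0.008 in the hazard ratio, both in the extreme row. The Monte Carlo standard error of a single power figure near 85% is √(0.85 × 0.15 / 1500) = 0.9 points. For a type I error near 5% it is √(0.05 × 0.95 / 1500) = 0.6 points. The models share datasets, so the differences between them are more precise than these figures suggest.

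Power exceeds 80% because patients who leave early still contribute follow-up, whereas the plan's 20% inflation treats them as lost entirely.

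**The case against.** The strongest reply is that this is loose wording. The rule itself matches the randomisation, the list after it may be only a gloss, and *study site* is never defined. The Study design section speaks of study hospitals, so *study sites* could mean the wards. That is possible, and if so the remedy is a change of terms. It does not remove the point: the abstract counts two clinical sites and the Settings section counts four wards in two hospitals, so a literal reader fits two levels.

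A second reply is that site may capture most of what matters. If the emergency ward is the only ward in its hospital, the site term carries the emergency-versus-cardiac contrast exactly, and differences between hospitals are captured under any split. This stands, and it is one reason why the effect is small.

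Some stronger readings are tempting, but the documents do not support them:

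- A reader might infer that the primary model is wrong or the test invalid. In every scenario tried, type I error stayed near 5% with either covariate. The model contradicts its own rule; it does not give invalid inference.
- A reader might infer that emergency patients are being pooled with elective patients. The eligibility criteria admit both emergency and elective procedures but assign neither to a ward, and no ward event rates are given.
- A reader might take the unstratified chi-square test as part of the same fault. It remains valid after stratified randomisation, if slightly conservative. Whether it or the Cox model is primary is a separate question.
- Further baseline covariates such as age or index presentation would be a preference, not the correction of an error. The plan contains no log-rank test to which strata could be applied.

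**Conclusion.** The inconsistency is certain from the text: one section stratifies by ward and smoking status, and the other reports the stratification factors as site and smoking status. One of them needs correcting.

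The consequence is minor. Taken literally, the analysis gives up about 0 to 2 points of power and attenuates the hazard ratio by about 0.00 to 0.01. These sizes rest on assumed ward risks, ward sizes, smoking prevalence and ward-to-hospital assignment; the upper end needs a six-fold difference in risk (4% against 24%) between two wards of one hospital. The sample sizes of 752 and 940 per group stand. The correction is worth making because it is almost free and leaves only one reading of the model.

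**What to change.** In Data analyses, replace *study sites* with *ward (four levels)*, so that the Cox model adjusts for ward and smoking status as used in the randomisation. Ward may enter as a covariate or as strata; either follows the design. If randomisation was in fact stratified by hospital, leave the analysis text and correct Randomization and blinding instead.

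The cost is one line. Ward must already be recorded for each patient because it is a randomisation stratum, and as a covariate it adds two parameters against about 120 events in one pairwise comparison. The section Study status and recruitment says that data cleaning and analysis had not begun at submission. Provided that is still so when the text is amended, the change can be made without sight of results. No other figure in the plan changes.

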Self-efficacy		X			X	X	X	X
Effectiveness perception		X			X	X	X	X
Intention		X			X	X	X	X
Motivation		X			X	X	X	X
Volition		X			X	X	X	X
Stages of behavior change^a^		X			X	X	X	X
Knowledge of CHD		X			X	X	X	X
Perceived importance of health behaviors		X			X	X	X	X

CHD, coronary heart disease. −T1: Start point for patient recruitment; T0: Baseline; T_1_: 1 month; T_2_: 3 months; T_3_: 6 months; T_4_: 12 months; T_5_: 24 months; T_6_: 36 months

^a^The stages of behavior change, mediators and moderators of behavior change will be assessed dynamically

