
**Table 2 Tab2:** The secondary outcomes and related measurements assessed in the iCARE study

Secondary outcomes	Measurements or tools
*Health behaviors*	
Dietary intake	A Short Food Frequency Questionnaire (FFQ) which was developed for this study according to the Chinese Guidelines on Cardiovascular Disease Prevention [43, 44]
Physical activity	The Simplified Chinese Version of the International Physical Activity Questionnaire (IPAQ) [45]
Smoking status	A 32-item Smoking Status Questionnaire which was developed for this study according to smoking history questionnaire from Lv et al. [44]
Medication adherence	A validated 8-item Chinese version of Morisky Medication Adherence Scale (C-MMAS-8) ^a^ [50, 51]
Cardiovascular health	American Heart Association Cardiovascular Health Score [8]
Anthropometry parameters	A Baseline Assessment Questionnaire (A) which was developed for this study
Biochemical parameters	Collected through follow-up visits with a Follow-up Assessment Questionnaire which was developed for this study and confirmed by reviewing medical records
All-cause mortality	Collected through follow-up visits with a Follow-up Assessment Questionnaire which was developed for this study and confirmed by reviewing medical records
All-cause readmission	Collected through follow-up visits with a Follow-up Assessment Questionnaire which was developed for this study and confirmed by reviewing medical records
Frequency of medical treatment	Collected through follow-up visits with a Follow-up Assessment Questionnaire which was developed for this study and confirmed by reviewing medical records
Patients’ engagement in the intervention	Data derived from iCARE platform: (1) the number of screens patients visited, (2) the frequency in uploading data, and (3) the number of interventions they accessed while using the patient application
Cardiovascular risks	10-year Framingham risk scores of cardiovascular risks tool [59]
*Mediators and moderators*	
Risk perception	A 4-item Risk Perception on Cardiovascular Risks Scale which was adapted from Renner and Schwarzer [60]
Outcome expectation	Outcome Expectation of Healthy Diet Scale, Outcome Expectation of Regular Exercise Scale, and Outcome Expectation of Quitting Smoking were from Renner and Schwarzer [60]. Outcome Expectation of Medication Management Scale was developed for this study

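### The blanket model choice for secondary outcomes does not suit all-cause mortality, a once-only event under incomplete follow-up; a time-to-event analysis should be named for it

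*Protocol article*

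**What the plan says.** Data analyses gives one modelling rule for the secondary outcomes as a class: "The mixed models and multilevel logistic regression models will be used to assess the differences in secondary outcomes between groups". It makes no exception. Just before this it states "All analyses related to secondary outcomes of the study are exploratory", and it gives as examples "changes in the proportion of adherence to health behaviors and medication, changes in anthropometry and biochemical parameters, etc".

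Table 2 (Secondary outcomes) lists "All-cause mortality", described as "Collected through follow-up visits with a Follow-up Assessment Questionnaire which was developed for this study and confirmed by reviewing medical records". Table 1 marks it at all six follow-up points: "T_1_: 1 month; T_2_: 3 months; T_3_: 6 months; T_4_: 12 months; T_5_: 24 months; T_6_: 36 months".

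A survival method appears in the same section, but for the primary outcome only: "Cox proportional hazards regression (with time to first event) will be used to estimate hazard ratios (HRs) comparing MACEs among three groups".

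The sample size section adds: "we anticipated a maximum attrition rate of 20% among all enrolled patients".

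**The concern.** Mixed and multilevel logistic models suit outcomes that can move up or down from visit to visit, such as smoking, adherence, weight or lipids. Death is different: it happens once and cannot reverse. An analysis of it has to count each death once and deal with patients whose follow-up ends early. The stated rule secures neither, although the Cox model that does both is named in the same section for MACEs.

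All-cause mortality has some weight here. The composite counts only deaths attributed to cardiovascular disease, the trial is open-label, and the plan intends the secondary results to help in reading the primary one. All-cause mortality is the natural check on the composite, so its estimate should be interpretable.

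**Working it through.** **The plan's own figure.** The article gives no figure for mortality; its only calculation concerns MACEs. Required events for a hazard ratio of 0.6, two-sided alpha 0.05 and 80% power: 4 × (1.960 + 0.842)² / (ln 0.6)² = 120.3. Dividing by the mean event rate (10% + 6%)/2 = 8% gives 1,504 patients in two arms, or 752 per group. Then 752/0.8 = 940 per group and 2,820 in all. The stated figures are reproduced, and this point does not touch them.

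**Inputs.** From the article: visits at 1, 3, 6, 12, 24 and 36 months, 940 per arm, attrition up to 20%. Assumed, because the article gives no rate: 3-year all-cause mortality of 2% to 8%.

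The article does not say how mortality enters the model. Three layouts fit its sentence.

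**Layout 1: status carried forward over T1 to T6, with a patient random intercept.** A death in month 4 is recorded as 0, 0, 1, 1, 1, 1 (four event rows); a death in month 30 gives one. Under a constant hazard at low mortality, deaths fall in the six intervals roughly in proportion to their lengths of 1, 2, 3, 6, 12 and 12 months. Rows per death average (1×6 + 2×5 + 3×4 + 6×3 + 12×2 + 12×1)/36 = 82/36 = 2.28.

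| Assumed 3-year mortality | Deaths per arm of 940 | Event rows per arm |
|---|---|---|
| 2% | 19 | 43 |
| 3% | 28 | 64 |
| 5% | 47 | 107 |
| 8% | 75 | 171 |

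Three two-arm data sets were simulated (940 per arm, assumed 5% control mortality, hazard ratio 0.6). Each was fitted with a random-intercept logistic model on carried-forward rows, using 7, 15, 31 and 61 quadrature nodes, and with a plain logistic model by visit whose rows stop at death.

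| Data set | Deaths (control, intervention) | Log rate ratio | Carried forward: log odds ratio at 7, 15, 31, 61 nodes | Rows ending at death: log odds ratio |
|---|---|---|---|---|
| 1 | 44, 26 | −0.53 | 0.07, −0.21, −0.11, −4.77 | −0.53 |
| 2 | 55, 31 | −0.58 | −0.49, −1.07, −1.18, −7.90 | −0.59 |
| 3 | 45, 30 | −0.41 | −2.66, −0.62, −0.35, −8.46 | −0.42 |

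In the carried-forward fits the random-intercept standard deviation rose from about 15–22 at 7 nodes to 43–45 at 61, and the group effect never settled. Near-perfect repetition within patients leaves the model with nothing to anchor that variance.

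**Layout 2: one 36-month status per patient, with ward or site as the level.** Each death counts once, but there is no censoring. At the anticipated maximum, 0.20 × 940 = 188 patients per arm have no 36-month status and must be dropped or assumed alive. Against 75 to 19 deaths (8% to 2% mortality), losses outnumber deaths by 188/75.2 = 2.5 to 188/18.8 = 10 times.

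**Layout 3: rows ending at death or loss.** Each death counts once and time at risk is respected on the visit grid. The simulated estimates in the last column above, where rows stopped at death and no losses were simulated, track the log rate ratios, with standard errors of 0.23 to 0.24. This is a discrete-time survival model.

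**The case against.** The strongest reply is that the fault lies in a data layout the article never states. A reader might infer that the plan counts one death again at every later visit, so that its mortality result must be unstable and uninterpretable. The documents do not support that. The marks in Table 1 show when mortality is ascertained, not how it is coded. Nothing says that rows continue after death, and a dead patient has no later visits. The levels are not defined as visits within patients either: patients come from four wards in two hospitals, so one record per patient within ward fits the sentence equally well. The extreme carried-forward estimates also depend on the number of quadrature nodes; they show numerical failure, not a result that the trial would report.

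The examples given are adherence, anthropometry and biochemistry, so the sentence was probably written with repeated measures in mind. An article may also leave the data layout to the full protocol or analysis plan.

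All of this limits the claim. What remains is that the article does state a method, without exception, for a class that includes all-cause mortality, and names the suitable method for MACEs only. That is an ill-fitting stated choice, not merely missing detail.

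The objection is right about readmission. It can recur, so a repeated-measures model is defensible, and preferring time to first readmission would be a matter of taste.

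**Conclusion.** The point holds as a low-stakes improvement. The stated rule puts a once-only event under models suited to repeated measures. Of the three layouts it permits, one gives an unstable group effect, one has no way to handle up to 188 losses per arm, and the third works because it is in effect a survival analysis. The plan does not say which is meant, so a claim that it does multiply deaths would go too far.

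The 2.28 rows per death assumes a constant hazard. The mortality rates and the hazard ratio for death in the simulations are assumptions, and three data sets illustrate instability without measuring a bias. Secondary analyses are declared exploratory, and the primary analysis and sample size are unaffected.

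**What to change.** In Data analyses, limit the mixed and multilevel logistic models to repeatedly measured outcomes: behaviours, adherence, anthropometry and laboratory values. Add one sentence: all-cause mortality will be analysed with the same stratification-adjusted Cox model as MACEs, or an equivalent discrete-time hazard model, with patients censored at last contact. The analysis of readmission may stay as planned.

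The cost is a sentence or two. The article does not say outright that dates of death are recorded. However, the planned Cox model for MACEs already needs the date of a cardiovascular death, and the date of any other death as a censoring time, so no new data should be needed. Censoring at last contact still assumes that loss is unrelated to the risk of death; the change makes that assumption explicit but does not remove it.
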